**Methods:**

Sixty patients will be randomized to receive nonsurgical care or IMPACT. After 9 months of nonsurgical care, patients in the control group are allowed to receive IMPACT surgery. The Knee Injury and Osteoarthritis Outcome Score (KOOS), pain (numeric rating scale, NRS), and EuroQol five dimensions five levels (EQ5D-5 L) will be used to compare outcomes at baseline and 3, 6, 9, 12, and 18 months after inclusion. Cartilage formation will be assessed at baseline, and 6 and 18 months after inclusion using MRI. An independent rheumatologist will monitor the onset of a potential inflammatory response. (Severe) adverse events will be recorded. Lastly, the difference between IMPACT and nonsurgical care in terms of societal costs will be assessed by monitoring healthcare resource use and productivity losses during the study period. A health economic model will be developed to estimate the incremental cost-effectiveness ratio of IMPACT vs. nonsurgical treatment in terms of costs per quality adjusted life year over a 5-year time horizon.

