#### Primary exclusion criteria (at the outpatient clinic)

If the patients meet any of the following criteria at the screening visit, they will not be eligible for the study:
Malalignment of > 5° (correctional osteotomy is allowed during the trial).(History of) OA, defined as Kellgren-Lawrence grade ≥ 3 as determined from appropriate radiography.Joint instability (ligament reconstruction is allowed during the trial).Concomitant inflammatory disease that affects the joint (rheumatoid arthritis, metabolic bone disease, psoriasis, gout, symptomatic chondrocalcinosis).(History of) Septic arthritis.(History of) Total meniscectomy in the target knee joint.Any surgery in the index knee joint 6 months prior to study inclusion.Risk groups for MRI due to the magnetic field such as patients with pacemakers, nerve stimulators, metal particles, stents, clips or implants, (possible) pregnancy, or breastfeeding.

Definitive eligibility is assessed during surgery based on the criteria below.

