## Interventions

### Intervention description {11a}

IMPACT is a one-stage cell-based regenerative therapy for isolated articular cartilage lesions. The investigational product consists of 10% autologous chondrons recycled from the debrided defect tissue and 90% allogeneic MSCs in Tisseel® tissue glue (Baxter B.V, Utrecht, the Netherlands) which will act as a cell carrier for implantation. The MSCs are obtained from the bone marrow of healthy non-HLA matched donors in the GMP-licensed Cell Therapy Facility (Department of Clinical Pharmacy, University Medical Center Utrecht) and cultured and characterized as described previously [22]. To summarize, the bone marrow aspirate is density-separated and MSCs are isolated using plastic adherence. The MSCs are expanded up to passage three after which they are cryopreserved. MSCs are characterized by the expression of CD73, CD105, and CD90 and the absence of expression of CD45, and CD3.

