### Outcomes {12}

The primary outcome is the comparison in total KOOS between patients with cartilage defects that are treated with IMPACT and patients treated with standard care (nonsurgical treatment) until 9 months after randomization. Total KOOS is an average of the scores in the five subscales of KOOS [23]. Other outcomes of interest are outcomes in the five subscales of KOOS, pain (numeric rating scale, NRS), general health (EuroQol five dimensions five levels, EQ5D-5 L), and structural repair (MRI). After 9 months, patients in the nonsurgical group are allowed to undergo IMPACT surgery, this will be regarded as failed nonsurgical treatment, and the time of crossover will be recorded. Change from baseline assessed with the KOOS of the total group of patients treated with IMPACT at 3, 6, 9, 12 and 18 months after treatment will be evaluated (per protocol). The potential effect of time until surgical treatment will be assessed. Clinical safety will be determined by active tracing of the adverse event rate observed after IMPACT and nonsurgical therapy. Additionally, emergence of an immune response will be assessed by screening for anti-HLA antibodies in peripheral blood preoperatively and 4 weeks postoperatively. The HLA phenotype of MSC donors will be compared to newly formed anti-HLA antibodies. Societal costs will be assessed by monitoring the costs related to the IMPACT procedure and the accompanying rehabilitation period, as well as costs related to nonsurgical (or delayed) treatment. In this analysis, two scenarios will be compared: (I) IMPACT vs. nonsurgical treatment and (II) IMPACT vs. delayed surgical treatment. In the first scenario, it is assumed that patients randomized to nonsurgical treatment will not undergo IMPACT in the next 5 years, whereas the second scenario includes patients who were randomized to nonsurgical care and opt for IMPACT after 9 months follow-up. In both scenarios, costs of other healthcare-related resource use (including physiotherapy, home care, medication use, and costs related to adverse events), as well as costs attributable to health-related work leave (i.e., productivity losses), will be collected over a follow-up period of (at least) 9 months. For nonsurgical treatment, health outcomes (from the EQ-5D-5L) and costs within the first 9 months will be extrapolated to calculate costs/QALY over a 5-year time horizon. Similarly, health outcomes and costs for (delayed) IMPACT will also be extrapolated to a five-year time horizon, using results from the completed phase I/II study (unpublished results).

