
### Participant timeline {13}

Table 1 shows the participant timeline.

**Table 1 Tab1:** Participant timeline

**Outpatient Clinic:** Screening (MRI) Study information provided in writing	
**Baseline visit:** Informed consent Baseline study MRI Randomization Baseline PROMs	
Group A: IMPACT	Group B: Control (nonsurgical)
**Preoperative screening** Anti-HLA antibodies	**3 months after inclusion** PROMs Check-up study physician (by telephone)
**Surgery/1 day postoperative** Blood chemistry (CRP, ESR, Leucocytes) Visit physical therapist Check-up rheumatologist Check-up study physician	**6 months after inclusion** PROMs Check-up study physician MRI
**1 week postoperative** Blood chemistry (CRP, ESR, Leucocytes) Check-up rheumatologist Check-up study physician	**9 months after inclusion** PROMs
**4 weeks postoperative** Blood chemistry (CRP, ESR, Leucocytes, anti-HLA antibodies) Check-up rheumatologist Check-up study physician	In case of cross-over to IMPACT: follow group A In case nonsurgical treatment is continued: **12 months after inclusion:** PROMs
**3 months postoperative** Check-up study physician (by telephone) PROMs	**18 months after inclusion:** PROMs MRI
**6 months postoperative** Check-up study physician PROMs MRI	
**9 months postoperative** PROMs	
**12 months postoperative** Check-up study physician PROMs	
**18 months postoperative** Check-up study physician PROMs MRI	

*CRP* C-reactive protein, *ESR* erythrocyte sedimentation rat, *HLA* human leukocyte antigens, *IMPACT* Instant MSC Product accompanying Autologous Chondron Transplantation, *MRI* magnetic resonance imaging; *PROMs* patient-reported outcome measures

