## Discussion

This randomized controlled trial is designed to investigate efficacy of IMPACT compared to nonsurgical care. Safety of IMPACT one-stage surgery for articular cartilage defects will be monitored in 30 to 60 patients. Also, cost-effectiveness of IMPACT will be compared to nonsurgical care.

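### The donor comparison covers only newly formed anti-HLA antibodies, so a rise after implantation in an antibody already directed at the MSC donor would not be attributed to the product

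*Protocol article*

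**What the plan says.** Outcomes {12} gives the aim and the sampling in one sentence: "emergence of an immune response will be assessed by screening for anti-HLA antibodies in peripheral blood preoperatively and 4 weeks postoperatively". The next sentence defines the link to the product: "The HLA phenotype of MSC donors will be compared to newly formed anti-HLA antibodies". No other comparison between patient antibodies and donor phenotype appears in the article.

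Intervention description {11a} explains why that link matters: "The MSCs are obtained from the bone marrow of healthy non-HLA matched donors". Table 1 under Participant timeline {13} places one anti-HLA sample at preoperative screening and one at the 4-week visit, listed as "Blood chemistry (CRP, ESR, Leucocytes, anti-HLA antibodies) Check-up rheumatologist Check-up study physician". Control patients who cross over follow the same schedule.

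None of the eligibility lists, primary or definitive, mentions existing anti-HLA antibodies. The closest exclusion concerns joint disease ("Concomitant inflammatory disease that affects the joint (rheumatoid arthritis, metabolic bone disease, psoriasis, gout, symptomatic chondrocalcinosis"). Pregnancy appears only as a current state, among the MRI risk groups.

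The Strengths section presents the anti-HLA screening as a source of insight into how MSCs behave in the body, transferable to other uses of these cells.

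**The concern.** The aim is to detect an emergent immune response. In a recipient of unmatched allogeneic cells, such a response can take two serological forms: a new antibody against a donor antigen, or a rise in an antibody against a donor antigen that the patient already had. The stated comparison names only the first. On the ordinary meaning of the words, an antibody already present in the preoperative sample is not newly formed. It therefore never reaches the comparison with the donor, even if its level climbs after implantation.

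Two pieces of information are at stake:

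- **Attribution.** A rise in donor-directed antibody is a response to the product. Without the donor comparison it cannot be identified as one.
- **Baseline risk.** Whether a patient already carried antibody against the donor used is a natural variable to set against synovitis, prolonged swelling and the other adverse events of interest. The preoperative sample could show this, but as described it serves only to subtract what was there before.

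This is the only donor-specific immune measure that the article describes, in a trial that treats at most 60 patients.

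**Working it through.** The plan gives no figure on this point to reproduce. The check is a reading of the stated rule case by case, followed by an illustration of scale on assumed rates.

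**Step 1: the rule applied to four antibody patterns.** The antibody in rows 2 to 4 is directed at an HLA antigen of the MSC donor used.

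| Pattern | Before surgery | 4 weeks | Emergent response? | Donor comparison as written? |
|---|---|---|---|---|
| 1. No antibody | absent | absent | no | not needed |
| 2. New antibody | absent | present | yes | yes |
| 3. Existing antibody, stable | present | present, unchanged | no | no |
| 4. Existing antibody, rising | present | present, higher | yes | no |

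Pattern 4 is the gap in the outcome: an emergent response without a donor comparison. In pattern 3 no outcome is lost, because nothing has emerged; what is lost is a baseline characteristic.

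**Step 2: can patterns 3 and 4 occur?** Donors are unmatched (Intervention description {11a}) and no listed criterion removes patients with prior antibodies. Nothing in the article prevents either pattern.

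**Step 3: how many patients could be involved?**

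Inputs:
- N, patients treated with IMPACT: 30 to 60, from the Discussion ("Safety of IMPACT one-stage surgery for articular cartilage defects will be monitored in 30 to 60 patients").
- p, proportion with antibody against the donor used before surgery: not in the article. Assumed at 1%, 5% and 10%.
- r, proportion of those whose antibody rises by 4 weeks: not in the article, anywhere from 0 to 1.

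Formulas: expected carriers = N × p; chance of at least one carrier = 1 − (1 − p)^N; expected missed rises = N × p × r.

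| Assumed p | Expected, N = 30 | Expected, N = 60 | Chance of at least one, N = 30 | Chance of at least one, N = 60 |
|---|---|---|---|---|
| 1% | 30 × 0.01 = 0.3 | 60 × 0.01 = 0.6 | 1 − 0.99^30 = 26% | 1 − 0.99^60 = 45% |
| 5% | 30 × 0.05 = 1.5 | 60 × 0.05 = 3 | 1 − 0.95^30 = 79% | 1 − 0.95^60 = 95% |
| 10% | 30 × 0.10 = 3 | 60 × 0.10 = 6 | 1 − 0.90^30 = 96% | 1 − 0.90^60 > 99% |

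The expected columns count patterns 3 and 4 together. Missed rises equal these figures multiplied by r, so they lie between zero and the figure shown. The assumed p concerns antibody against the donor used. The proportion with any anti-HLA antibody is at least as large and would overstate the problem.

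**The case against.** Four arguments can be made against the point.

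1. **No misclassification rule exists.** A reader might infer that a previously sensitised patient is counted as a non-responder, and that the response rate is biased downward. The article does not support this. It defines no responder and no responder rate, and the screening itself covers anti-HLA antibodies at both times. This objection stands: the supportable statement is that a rise is not linked to the donor, not that the patient is scored negative.

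2. **A stable existing antibody is rightly not an outcome.** A reader might treat every previously sensitised patient as a missed response. The stated aim is emergence, and an unchanged antibody has not emerged. This also stands and confines the outcome gap to pattern 4.

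3. **The term is undefined and the detail may lie elsewhere.** The article does not say whether newly formed means a new specificity only or also a marked rise. The full protocol or analysis plan, not shown, may settle this along with the assay and thresholds. This stands in part. Assay details are not expected in an article, but the article does state which antibodies are compared with the donor, and on their plain meaning its words leave existing antibodies out.

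4. **Other immune monitoring continues.** The abstract says "An independent rheumatologist will monitor the onset of a potential inflammatory response", and Table 1 pairs rheumatologist check-ups with CRP, ESR and leucocytes. There is also an algorithm for foreign body responses, safety-officer review of SAEs, and synovitis among the adverse events of interest. None depends on antibody status, so a clinically evident reaction would be recorded. This limits the consequence. It does not close the gap, because none of these measures is donor-specific, and raised CRP or swelling after a mini-arthrotomy also has ordinary surgical causes.

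**Conclusion.** The point holds in a narrow form. As worded, the donor comparison omits antibodies present before surgery. A post-implantation rise in an existing donor-directed antibody would therefore not be attributed to the product, and pre-existing donor-directed antibody would not be examined as a baseline risk factor.

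The size cannot be fixed from the document. On an assumed 1% to 10%, between 0.3 and 6 treated patients would be expected to carry such an antibody, and only those with a rise would be missed, possibly none. In a cohort of 30 to 60, even one or two unattributed responses would matter to a reported donor-specific rate.

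The conclusion rests on the plain meaning of newly formed and on the eligibility lists as published. If the full protocol defines the term to include rises, only the baseline comparison remains to be added. Severity is minor: this is an additional safety outcome, with no bearing on the primary KOOS analysis or the sample size.

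**What to change.** Reword the donor comparison in Outcomes {12} and carry it into the analysis plan:

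- Compare the anti-HLA specificities in both the preoperative and the 4-week sample with the HLA phenotype of the donor whose cells the patient received.
- Report two kinds of emergent response: newly formed donor-specific antibody, and a rise in pre-existing donor-specific antibody, with the size of rise that counts fixed in advance.
- Report stable pre-formed donor-specific antibody as a separate baseline class, not as a response.
- Where possible, test each patient's two samples in the same assay run, so that a rise is not confused with variation between runs.
- Tabulate the adverse events of interest by class, descriptively and without testing, given the small numbers.

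Both blood samples are already in the schedule, so no visit or draw is added. The cost is storing preoperative serum until the 4-week sample arrives, plus slightly more laboratory and analysis work.

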Both in vitro and in vivo cartilage formation has been shown to improve by direct contact between multipotent mesenchymal stromal cells (MSCs) and articular chondrocytes [16–20]. This stimulatory effect on cartilage matrix formation further increases when MSCs are combined with chondrons (chondrocytes with their pericellular matrix) [19]. Using this combination of cells allows for a one-stage application, as autologous cells can be used without expansion. “Instant MSC Product accompanying Autologous Chondron Transplantation” (IMPACT) combines 10% autologous chondrons with 90% allogeneic MSCs in a single surgery for the treatment of cartilage defects. Compared to the two-stage ACI procedure, IMPACT decreases the patient burden and significantly reduces the costs of treatment [13]. Safety, feasibility, initial efficacy, and structural tissue repair of IMPACT was shown in a cohort of 35 patients with cartilage lesions (3.2 ± 0.7 cm) (NCT02037204) [21, 22].

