### Trial design {8}

In this phase III randomized controlled clinical trial, IMPACT is compared to nonsurgical treatment. The patient allocation ratio is 1:1. Patients in the nonsurgical group are allowed to cross over to the treatment group after 9 months follow-up.

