## Statistical methods

### Statistical methods for primary and secondary outcomes {20a}

Data will be analyzed using IBM SPSS (version 15.0.0.2, Chicago, IL). Data from the primary objective (KOOS, EQ-5D-5L) will be presented as continuous variables. To compare between the two treatment groups, a mixed model analysis will be performed, with treatment group and assessment date of the PROMs (e.g., baseline, 3 months, 6 months) as fixed factors. Differences will be considered statistically significant for the fixed effect of treatment groups if *p* < 0.05 [30]. The 95% confidence interval of the fixed effect size will be used to assess whether treatment difference reaches the minimally clinical important difference.

T1rho-scores will be calculated from the biochemical MRI scans; differences in T1rho-scores will be compared between the time points *t* = 0 (at inclusion before IMPACT or nonsurgical treatment) and *t* = 6 and 18 months after inclusion or surgery. Differences will be compared using Student’s *t* test. The differences in T1rho-score will be tested for normality using Q–Q plots. *P* values less than 0.05 will be considered significant. We will calculate the ICERs of IMPACT vs. nonsurgical treatment and vs. delayed surgical treatment in terms of cost/QALY over a 5-year time horizon. The effect of uncertainty in input parameters on the ICERs will be calculated by means of one-way sensitivity analysis as well as probabilistic sensitivity analyses using Monte Carlo simulation.

All (S)AE(I)s will be summarized and recorded including the nature, date and time of onset, date of resolution, determination of seriousness, severity, action taken, outcome, and possible causality to study treatment. SAE data will be presented in a descriptive manner.

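### In scenario I the 5-year ICER projects controls from their own 9 months but IMPACT with help of an earlier cohort, and the planned sensitivity analyses test neither that choice nor how long the benefit lasts

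*Protocol article*

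**What the plan says.** The protocol article plans ICERs "in terms of cost/QALY over a 5-year time horizon" (Statistical methods {20a}) for two scenarios, set out in Outcomes {12}. Scenario I compares IMPACT with nonsurgical care and assumes that controls have no IMPACT surgery for 5 years. Scenario II compares IMPACT with delayed IMPACT.

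The two treatments are projected from different sources. For nonsurgical care, "health outcomes (from the EQ-5D-5L) and costs within the first 9 months will be extrapolated to calculate costs/QALY over a 5-year time horizon". Outcomes and costs for (delayed) IMPACT "will also be extrapolated to a five-year time horizon, using results from the completed phase I/II study", whose results are marked as unpublished. Background {6a} describes that study only as one in which safety, feasibility and initial efficacy "was shown in a cohort of 35 patients with cartilage lesions". It mentions no comparator.

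Trial design {8} sets the limit of the randomised contrast: "Patients in the nonsurgical group are allowed to cross over to the treatment group after 9 months follow-up". The trial itself goes further. Objectives {7} and Table 1 give IMPACT patients at least 18 months of follow-up, with questionnaires at 12 and 18 months. Controls who stay nonsurgical also have 12- and 18-month questionnaires.

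On uncertainty, Statistical methods {20a} says: "The effect of uncertainty in input parameters on the ICERs will be calculated by means of one-way sensitivity analysis". It adds probabilistic analysis by Monte Carlo simulation.

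**The concern.** A 5-year ICER needs extrapolation. The question is what the extrapolated difference is made of. In scenario I, one side is carried forward from unblinded controls observed for 9 months, who know that surgery then becomes available. The other side is carried forward with results from a different set of patients. If those patients had higher or lower utilities or costs than the randomised IMPACT arm, or if they changed after month 9 for reasons that controls would share, the gap would be counted as an effect of IMPACT. Randomisation does not protect against this.

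The named sensitivity analyses would not reveal it. Random draws around cohort-based inputs describe sampling error in those inputs. They do not ask whether the cohort is the right source, or whether the benefit lasts. The 5-year ICER is a stated objective, so a reader needs to see how far it depends on both.

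**Working it through.** The article gives no figure for the ICER or for the extrapolated share of the horizon, so there is none to reproduce.

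**Step 1: share of the horizon.** Inputs: horizon 60 months (Statistical methods {20a}); crossover allowed after month 9 (Trial design {8}); IMPACT follow-up of 18 months (Objectives {7}). Share after month t = (60 − t)/60.

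- After month 9: 51/60 = 85%.
- After month 18: 42/60 = 70%.
- Months 9 to 18, with trial data on the randomised IMPACT arm: 9/60 = 15%.

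With assumed annual discount rates of 1.5% to 5%, the first share becomes 84.5% to 83.4% and the second 69.2% to 67.4%. The part that may rest on the cohort is thus 70% if it takes over at month 18 and 85% if it takes over at month 9. The article does not say which.

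**Step 2: persistence of benefit (illustration).** Assumptions, not document figures: utility difference of 0.05 at month 9, reached linearly from zero; no discounting.

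- Months 0 to 9: 0.5 × 0.75 × 0.05 = 0.019 QALY.
- Maintained to year 5: 0.05 × 4.25 = 0.2125; total 0.231.
- Linear waning to zero at year 5: 0.5 × 0.05 × 4.25 = 0.106; total 0.125.
- None after month 18: 0.05 × 0.75 = 0.0375; total 0.056.

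**Step 3: source offset (illustration).** Assumption: utilities in the cohort differ by 0.03 from those in the randomised IMPACT arm throughout.

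- Cohort used from month 9: 0.03 × 4.25 = 0.1275, about 0.13 QALY.
- Cohort used from month 18: 0.03 × 3.5 = 0.105 QALY.

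Against the maintained total of 0.231, that is 45% to 55%. The shift has the sign of the offset, which is unknown.

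**Step 4: what the planned analyses cover.** Statistical methods {20a} names one-way and probabilistic analyses of input parameters. Scenarios I and II differ in whether controls later receive IMPACT. Neither the analyses nor the scenarios change the source of the IMPACT projection or how long its benefit lasts.

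**The case against.** The strongest reply is that any 5-year ICER from this design must be mostly extrapolated, that the article says so openly, and that informing the later course of a product from earlier data on the same product is normal modelling. This stands: the use of phase I/II data is not in itself an error. What remains is that only one arm's projection draws on it and that nothing named tests the choice.

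A second reply is that a fuller model plan, not shown, may contain structural scenarios, and that extrapolated utilities can be varied as inputs. This is possible, and it limits how firmly the gap can be stated. But the article itself fixes the sources and describes the sensitivity analyses as concerning input parameters.

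Some stronger readings are tempting but are not supported:

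- **That 85% of the horizon is a comparison with the cohort.** It is the share beyond month 9; the cohort-dependent part may be as low as 70%.
- **That the plan ignores the trial's own 12- and 18-month EQ-5D-5L.** The article is silent on their role in the projection. Its wording allows trial outcomes to be carried forward with help from the cohort.
- **That the cohort had smaller lesions than this trial.** The text gives a "cohort of 35 patients with cartilage lesions (3.2 ± 0.7 cm" as printed. Setting this against the 2–8 cm² entry range needs an assumed unit and an assumed normal distribution. The lesion sizes of this trial's patients are not known, and nothing in the article links size to EQ-5D-5L.
- **That both ICERs are affected alike.** In scenario II, immediate and delayed IMPACT draw on the same phase I/II source, so a source offset largely cancels.

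**Conclusion.** The point holds for scenario I. The arms are projected from different sources, the takeover month is open, and the named sensitivity analyses vary neither the source nor the persistence of benefit. That the cohort was uncontrolled is an inference from the absence of any mentioned comparator.

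The shares of 85% and 70% follow from the document's own time points. The QALY figures (0.231, 0.125 and 0.056; shift of 0.105 to 0.13) rest on assumed utilities without discounting and show only the order of size. A reader might infer from 0.231/0.056 = 4.1 that the planned ICER is wrong by a factor of four. That does not follow. The ratio holds only at equal incremental cost, although costs are extrapolated too. It also reflects assumed persistence, which affects any 5-year model whatever its source.

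The direction of any bias is unknown. The primary KOOS comparison is not affected. The change is worth making because it decides what the 5-year ICER can support.

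**What to change.** 1. State the takeover month. Use the randomised data to month 9 and the trial's own IMPACT EQ-5D-5L and costs to 18 months as the anchor, with costs as far as they are collected beyond the stated minimum of 9 months.
2. Use the phase I/II results only for the course after that, and check them against the trial's 12- and 18-month data.
3. Add structural scenarios to the one-way and Monte Carlo analyses: benefit maintained; waning to zero by year 5; none after 18 months; and the same post-9-month course in both arms. The last belongs among the scenarios and not in the base case. It freezes the 9-month difference, which amounts to the maintained-benefit case, while Intervention description {11a} has patients returning to sport only after that point.
4. Report the 9-month within-trial ICER beside the 5-year ICER.

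The cost is some extra modelling, with no new data collection, and a wider displayed range for the 5-year ICER.
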